### Measurements

At baseline, approximately one month before RYGB, and at clinical follow-up visits at 6, 12 and 24 months after RYGB, participants will be weighed and have their height measured. The women will, at baseline and at the follow-up visits, be asked to complete a number of questionnaires, sent to their home to fill in and return to KI by mail. The following questionnaires are used:

SF-36 [28] is measuring HRQoL (primary outcome) and is a widely-used instrument which measures health-related quality of life with 36 questions divided in eight dimensions: physical functioning, role limitations due to physical health problems, bodily pain, general health, vitality, social functioning, role limitations due to emotional problems and mental health. We also present data in a summary score for the physical components (PCS) and the mental components (MCS) including a cut off value of ≤42 for the MCS as having a risk for depression. The final scores for the different parts is made into a zero to 100 scale with higher numbers indicating better HRQoL.

Three-Factor Eating Questionnaire (TFEQ) [29] is a 21-item questionnaire measuring dietary restraint, emotional eating and uncontrolled eating. A higher score indicates higher restraint, uncontrolled eating and emotional eating [30, 31].

Body Esteem Scale (BES) [32] is a 23-item questionnaire measuring weight concerns, appearance and attribution. A lower score indicates worse body esteem.

Social Adjustment Scale (SAS) [33, 34] is a 45-item questionnaire measuring satisfaction with one’s social life in the different dimensions: work role, social and leisure activities, relationships with extended family, role as marital partner, parental role and role within the family unit. Lower scores indicates better social adjustment.

Disordered Eating after Bariatric Surgery (DEBS) [35] is a 7-item questionnaire which specifically measures disordered eating after bariatric surgery over the last 28 days. A higher score indicates a higher rate of disordered eating.

Furthermore, women will be asked to wear the validated GT3X+ accelerometer [36, 37] during all waking hours, for seven consecutive days, to objectively measure levels, patterns and intensity of PA and sedentary behavior [38] according to the latest definition, including intensity and posture [39]. Minimal wear time to qualify as a valid measurement is three weekdays and one weekend day with a minimum of ten hours wear time per day.

To be able to compare the intervention to no intervention the control group will receive the usual follow-up care, including weight measures at six and 12 months after RYGB, at the clinic where they had surgery, and like the intervention group, will be asked to complete the questionnaires, to wear the GT3X+ before and six, 12 and 24 months after RYGB. The usual follow-up care differs slightly between hospitals. However, in general it contains consultation with a dietitian about food intake after surgery, and appointments with a nurse and/or the surgeons to measure weight loss, results of laboratory tests and to ensure that no complications have occurred.

### Power calculations

Power calculations showed that 95 participants were needed in each group to attain a statistical power of at least 0.80 (based on HRQoL as the primary outcome), with an expected moderate effect size (Cohen’s d = 50), and alpha set at 0.05. Based on previous similar studies [25, 40], we expect 20% drop-out of patients during two years of follow-up. Thus, a minimum of 240 patients was required, and at final total of 259 participants were recruited and randomized either to the intervention (60%) or to usual care (40%).

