To reduce the problems associated with drop-out, a larger proportion (60%) of the participants were randomized to intervention. Unfortunately, 34% (*n* = 53) of the women in the intervention group did not attend any of the intervention sessions, even though they agreed to participate when invited and had completed the baseline assessments. This may have a negative effect on the upcoming results, but in accordance with the power calculations (see above), a minimum of 95 participants was needed to attain a statistical power of at least 0.80. In this trial 103 women (66%) in the intervention group completed the baseline assessments and attended at least one of the intervention session. Even so, the results may not be representative to the general Swedish women who undergo RYGB surgery.

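### The stated 95 per group does not follow from the stated inputs, which give 64, and the Discussion tests adequacy against 95 without the planned 20% drop-out

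*Protocol article*

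**What the plan says.** The Power calculations section of the protocol article states: "Power calculations showed that 95 participants were needed in each group to attain a statistical power of at least 0.80". It takes HRQoL as the primary outcome, "with an expected moderate effect size (Cohen’s d = 50", and "alpha set at 0.05". It continues: "we expect 20% drop-out of patients during two years of follow-up". From this it concludes: "Thus, a minimum of 240 patients was required". It reports 259 women randomized, 60% to the intervention and 40% to usual care. The Abstract and Baseline data give the arms as 156 and 103.

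The Discussion acknowledges that 34% of the intervention arm attended no session. It then recalls that "a minimum of 95 participants was needed to attain a statistical power of at least 0.80" and sets beside this the 103 intervention women who had baseline data and attended at least one session. Under Statistical analyses, those 103 women are the intervention side of the primary analysis.

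**The concern.** Three things do not fit together.

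- The printed effect size, 50, is impossible as a Cohen's d. Read as 0.50, the conventional moderate value, it does not lead to 95 per group at the stated alpha and power.
- The step from 95 to 240 treats the arms as equal, but the trial allocates 60:40.
- The Discussion uses 95 as its adequacy bar for a count taken before follow-up, although the power section treats 95 as the number needed before inflation for drop-out.

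At stake is whether a reader can tell for which effect, and at which significance level, the trial claims 80% power. The Background justifies the trial partly by its statistical power. If a stricter alpha lay behind 95, the threshold of the primary test would also change.

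**Working it through.** **Inputs.** From Power calculations: d = 0.50 (a reading of the printed 50), alpha 0.05, power 0.80, drop-out 20%, 95 per group, total 240. From Randomization: 60:40. From Baseline data: 156 and 103 randomized, 103 attenders. The article does not state sidedness; two-sided is assumed.

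**1. Does 95 follow?** The normal approximation is n per group = 2(z₁₋α/₂ + z₀.₈₀)² / d².

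- Alpha 0.05: 2(1.960 + 0.842)² / 0.25 = 62.8, so 63. The exact noncentral-t solution is 63.8, so **64**.
- A one-sided test gives 50 to 51. Power 0.90 gives 85 to 86, and power 0.95 gives 104 to 105. At 1.5:1 allocation about 53 to 54 controls and 80 to 81 intervention women are needed. Allowing for a rank test gives at most 67 to 74. None reproduces 95.
- 95 per group at d = 0.50 and alpha 0.05 has power **0.93**.

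**2. What would give about 95?**

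| Changed input | n per group |
|---|---|
| alpha 0.01 two-sided, d = 0.50, power 0.80 | 95.1 |
| d = 0.41, alpha 0.05, power 0.80 | about 95 |
| alpha 0.0167, power 0.85, d = 0.50 | 95.6 |
| design effect 95/64 = 1.48 on 64 | 95 |

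The article states none of these. The alpha 0.01 match is not quite exact either: 95.1 rounds up to 96, and 95 per group has power 0.799.

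**3. The total of 240.** 2 × 95 / 0.8 = 237.5, so 238, rounded up to 240. The drop-out step therefore reproduces, as an equal-arm calculation. At 60:40, 240 women give 144 and 96. If each arm loses 20% (an assumption; the article gives only an overall rate), controls remaining are 96 × 0.8 = 76.8, about 77. From the actual 103 they are 103 × 0.8 = 82.4, about 82. Both are below 95.

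**4. The Discussion's comparison.** Before loss, the bar that corresponds to 95 completers is 95 / 0.8 = 118.75, so 119. After loss, 103 attenders become about 82. The comparison is **103 against 119, or 82 against 95**, and 103 against 95 mixes the two.

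**5. Power after 20% loss in each arm (noncentral t).** All randomized women: 156 × 0.8 = 124.8, about 125, versus 82.

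| Set | d = 0.50, alpha 0.05 | d = 0.50, alpha 0.01 | d = 0.41, alpha 0.05 | Detectable d (alpha 0.05, power 0.80) |
|---|---|---|---|---|
| Attenders, 82 vs 82 | 0.89 | 0.72 | 0.74 | 0.44 |
| All randomized, 125 vs 82 | 0.94 | 0.82 | 0.82 | 0.40 |

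The second row makes no allowance for dilution by the 34% who attended no session.

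**The case against.** The best defence is that the error is on the safe side. With d = 0.50 and alpha 0.05, 95 per group does give power of at least 0.80; only the claim that so many were needed is wrong. Even 82 versus 82 has power 0.89. This stands. A reader might infer that the trial is underpowered, but the documents do not support that: a shortfall appears only if a stated input is replaced by one the article does not give.

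A reader might also infer that 95 is the alpha 0.01 sample size. That is a numerical match, not something the article says. A smaller effect fits as well. So does a design effect for sessions held in groups of about five, which a condensed article could have left out. Because the candidate explanations are not exhaustive, counting how many of them fall below 80% power proves nothing.

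Third, a reader might infer that the control arm could not keep 95 women. That holds only if controls lose about as many as the intervention arm. The Discussion says that more women were allocated to the intervention to reduce drop-out problems, which may mean that loss was expected mainly there. If all 48 losses (20% of 240) fell in the intervention arm, 96 versus 96 would remain. With 103 controls, a loss of up to 8 leaves at least 95. Such low control loss is optimistic and not stated, but it is not excluded.

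Finally, the Discussion is cautious: it allows that non-attendance may harm the results. It still offers 103 against 95 as its answer on power, and that comparison omits drop-out.

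**Conclusion.** The point holds as a misstated sample-size justification. Given d = 0.50, two-sided alpha 0.05 and power 0.80, the requirement is 64 per group, not 95, so the n or one of its inputs is wrong or missing. The article does not show which. The Discussion's comparison sets a count before follow-up against a requirement for completers; done consistently it fails the article's own bar of 95, yet it would clear a bar of 64 (82 against 64). The practical effect depends on which figure is wrong: attender-set power is 0.89 if the 95 is wrong, but 0.72 or 0.74 if alpha 0.01 or d = 0.41 was meant. These figures rest on reading 50 as 0.50, a two-sided t-test, and 20% loss in each arm.

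**What to change.** 1. Correct d to 0.50.
2. Either restate the requirement as 64 per group at two-sided alpha 0.05 (80 per group, 160 in total, with 20% drop-out at equal allocation), or state the input that produces 95, whether alpha, effect size or design effect. If it is a stricter alpha, the primary test must use it.
3. Report power for the actual 60:40 allocation after 20% loss, separately for the two sets. Planned attender set: about 82 versus 82, power 0.89 at d = 0.50 and alpha 0.05, detectable d 0.44. All randomized women: about 125 versus 82, power 0.94, detectable d 0.40, noting that this is before dilution by non-attenders. State the assumption of equal loss.
4. In the Discussion, replace 103 against 95 with a comparison that allows for drop-out: about 82 completers against whichever requirement is adopted.

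The cost is a text correction. No further enrolment is needed. The analysis changes only if a stricter alpha was intended. Some stated power may become less favourable if a stricter alpha or smaller effect proves to be the source of 95.

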### Randomization

Approximately two months after surgery 60% of the participants were block randomized to the intervention group (*n* = 163) and 40% to the control group (*n* = 103). One member of the research staff who was not currently working with the data collection was in charge of the randomization, which was computer generated randomization 60/40. The randomization was divided according to counties (Danderyd, Ersta and St Görans were randomized together, Uppsala and Örebro separately) in blocks of 5 participants and was carried out after date of surgery. Only RYGB participants with informed consent and baseline questionnaire data were randomized.

### Statistical analyses

The statistical analyses will focus on differences between the intervention and the control group from pre-surgery assessment to follow-up assessments at 24 months after RYGB. The women’s changes in weight will be taken into account in the analysis by stratification or adjustment. Primary analysis will be intention to treat analysis, including women who attended at least one session (*n* = 103). We will also conduct per protocol analysis including the women who have attended all four sessions (*n* = 33). We will also perform sensitivity analysis in order to detect any possible dose-response effects such as if the main outcomes will differ depending on if a woman have attended one, two three or all four sessions. Furthermore, individual factors, e.g. patient beliefs about causality of obesity, and contextual factors, e.g. variations in implementation of the intervention between centers for bariatric surgery, might moderate the effect of the intervention on health outcomes. These issues will be analyzed by mixed linear regression models or generalized estimation equations (GEE) to analyze repeated measurements over time. [41].

For the assessments of the baseline characteristics for the intervention and control group presented in this protocol, the analysis have been separated into women randomized to intervention group and women randomized to control. X^2^-tests were performed for categorical variables and t-tests for continuous variables, and because the majority of the continuous variables were not linear distributed, the Kruskal-Wallis test was used.

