## Background

Obesity with its health-related co-morbidities is a major public health problem world-wide [1]. However, lifestyle interventions, such as dietary restriction and increased physical activity (PA), have limited effect on weight loss and maintenance [2, 3]. On the other hand, Roux-en-Y Gastric Bypass (RYGB) surgery results in marked and sustained weight loss as well as improvements in obesity-related comorbidities, compared with lifestyle interventions [4]. In 2014, laparoscopic RYGB accounted for more than 80% of all approximately 7000 bariatric procedures performed in Sweden, of which 75% were women [5]. With the increased use of laparoscopic sleeve gastrectomy, the proportion of laparoscopic RYGB decreased to 64% of the bariatric procedures performed in Sweden 2016 [6].

Weight regain and reoccurrence of obesity related comorbidities after RYGB are not uncommon [7, 8]. In most cases, this is not caused by surgical issues [9], but rather by difficulties with adaptations to the psychosocial life changes brought about by the procedure [10], or by the patient’s inability to adhere to the prescribed lifestyle recommendations [9]. Patient’s health-related quality of life (HRQoL) and body esteem tend to improve, and is closely associated with weight loss, following RYGB [11, 12]. The improvement in HRQoL typically peaks during the first year after surgery, when the weight loss is most rapid, and then declines as gradual weight regain starts to occur at one to six years after surgery [11]. It is easy to imagine a negative spiral experienced by RYGB patients as their weight loss slows down or weight is regained. Shame and stigmatization lead to increased sedentary behaviors and avoidance of PA, which in its turn might induce even greater problems with body esteem and weight regain. It is therefore important to create efficient preventive measures to avoid this vicious circle.

There is a growing interest in the role of PA and sedentary behavior in achieving optimal weight loss and improving health outcomes after RYGB [13]. Participation in moderate to vigorous intensity PA and reduced sedentary time play an important role in body weight regulation and may contribute to improvements of surgical outcomes after RYGB [14, 15]. In addition, achieving sufficient amounts of PA after surgery is of importance for long-term all-cause and cardiovascular mortality [16] as well as weight maintenance [17].

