Although previous research suggests that dysfunctional eating behaviors, issues with body esteem and becoming habitually physically active represents a major challenge for many RYGB patients [10, 12, 18], few interventions to assist patients in meeting these challenges have been conducted. A 2015 systematic review and meta-analysis on interventions before and/or after bariatric surgery stated that the strength of evidence is limited by few trials, low methodological quality and short follow-up duration. The authors concluded that well-designed randomized controlled trials (RCTs) with at least two years follow-up are required. Previous RCTs evaluate weight-loss as the main outcome, with little focus on HRQoL and healthy levels of PA and sedentary behavior. This is of special concern as barriers to engage in PA and exercise, such as feeling too fat, is more common among obese adults [19]. In particular, RYGB patients frequently feel too overweight to exercise, or have fear of exercise-related injuries [15]. Hence, it may be appropriate to aim at reducing sedentary behavior after RYGB surgery, since reduced time spent sedentary may have beneficial effects on health and weight stability in populations with obesity, beyond the effects of light and moderate to vigorous PA (MVPA) [20, 21].

The need for an adequately powered RCT targeting patients undergoing bariatric surgery is justified for several reasons. Firstly, we are not aware of any theory-based counselling intervention for obese female patients after RYGB with appropriate statistical power. Secondly, as RYGB has been the most dominant bariatric procedure performed annually in Sweden during several years [6], it is timely to evaluate the effects of a novel theory-based post-bariatric intervention aimed at facilitating female patients’ psychosocial adjustment to daily life, including HRQoL, eating behavior, mood, body esteem, PA and sedentary behaviors. Such an intervention might also prevent further weight re-gain. Finally, a RCT is needed to evaluate the effects of an intervention, where the attainment of unbiased estimates is crucial and almost impossible to attain by observational studies.

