### Aim

This paper presents the study design and methodology of the “WELL-GBP” intervention (wellbeing after gastric bypass) and describes the baseline characteristics of the participating women. The “WELL-GBP” trial is targeting female RYGB patients in a health care setting to improve HRQoL and health related behaviors after RYGB. The overreaching goal of the current study is to find ways of optimizing the outcome for the RYGB patient, not only in terms of maintained weight loss but also in terms of HRQoL, eating behavior, body esteem, social adjustment, PA and sedentary behavior. The specific aims of the “WELL-GBP” trial are to answer the following questions within a randomized controlled trial:What are the effects of a dissonance-based intervention on HRQoL (primary outcome), eating behavior, body esteem and social adjustment of female RYGB patients 24 months after surgery?What are the effects of a dissonance-based intervention on objectively measured levels of physical activity and sedentary behavior of female RYGB patients 24 months after surgery?

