## Discussion

The ongoing RCT with a dissonance-based intervention, “WELL-GBP”, targeting female RYGB patients in a health care setting, aims to improve HRQoL and health-related behaviors after RYGB. The intervention is manual-based, free of charge, delivered in health care settings and could be delivered by health-care personnel such as nurses, dietitians, physiotherapists or counsellors, after some practice. We are not aware of any previous randomized controlled trial that has investigated the effects of a similar intervention on HRQoL and following RYGB.

Previous studies using dissonance-based interventions have had positive results on health outcomes and showed greater effect sizes compared to non-dissonance-based interventions or no intervention, regarding disordered eating, body dissatisfaction [24–26], and also increased PA at post-test, but not at 1–2 year follow-up [25, 26]. This trial uses a modified version of Stice’s dissonance-based prevention model and has been adapted to RYGB patients.

The women participating in this trial could be representative of women who undergo RYGB surgery in Sweden, as they are from different geographical areas and are similar in age and BMI at the time of surgery to other RYGB patients in Sweden [42]. They are also comparable in this respect to other bariatric patients from other parts of the world, although they tend to be slightly older and have a higher BMI [43]. A previous study comparing levels of PA pre-bariatric surgery measured by an accelerometer in Swedish women have similar characteristics in the different PA levels as the women in the “WELL-GBP” trial [44]. HRQoL in our sample was similar, although somewhat higher, than the general Swedish bariatric surgery patients [45]. HRQoL, especially PCS score, improves after bariatric surgery and is related to weight loss, gender and age, with lower PCS and MCS scores in women than men, and lower PCS but higher MCS with increased age [45].

The current “WELL-GBP” trial only includes Swedish-speaking women, as resources such as an interpreter at the group sessions were not feasible. This may affect the external validity as the future results will not be representative of women who live in Sweden but don’t master the Swedish language. Also, because this current trial only includes women, any possible intervention effect on men who undergo RYGB will not be possible to predict.

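### Weight change is to be adjusted for or stratified on without excluding change after randomisation; if the intervention affects weight, the result is not the total effect on HRQoL

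*Protocol article*

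**What the plan says.** All references are to the Protocol article.

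- **Statistical analyses.** The target is "differences between the intervention and the control group from pre-surgery assessment to follow-up assessments at 24 months after RYGB". The next sentence says that women's "changes in weight will be taken into account in the analysis by stratification or adjustment". The definition of the primary analysis follows. No interval for the weight change is given, no choice is made between the two methods, and no primary analysis free of weight change is named.
- **Randomization.** "Approximately two months after surgery 60% of the participants were block randomized to the intervention group".
- **Measurements.** Weight is taken at baseline, about one month before surgery, and then "at clinical follow-up visits at 6, 12 and 24 months after RYGB, participants will be weighed". No weight is scheduled at randomisation.
- **Background.** On the intervention: "Such an intervention might also prevent further weight re-gain". On HRQoL and body esteem after surgery, the improvement "is closely associated with weight loss, following RYGB".
- **Aim.** The overall goal is to optimise outcome "not only in terms of maintained weight loss but also in terms of HRQoL" and other domains. The first specific aim asks for the effect of the intervention on HRQoL, the primary outcome, 24 months after surgery.
- **Discussion.** "HRQoL, especially PCS score, improves after bariatric surgery and is related to weight loss, gender and age".

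**The concern.** The first aim asks what the intervention does to HRQoL at 24 months by whatever route, which is a total effect. Randomisation protects that comparison as long as the analysis conditions only on variables that allocation cannot have changed. Weight at 6, 12 and 24 months is not such a variable. By the article's own account it may lie on the path from intervention to HRQoL.

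Holding weight change fixed, by a covariate or by strata, asks a different question: how HRQoL differs between arms among women whose weight changed equally. Any benefit that runs through better weight maintenance is then taken out of the estimate. Women with equal weight change in the two arms also need not be alike in other causes of HRQoL. At stake is the primary estimate, and the harm arises in the case where the intervention helps with weight as the investigators hope.

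**Working it through.** The article gives no figure for this point that could be reproduced. The check therefore sets the timing and the stated pathway side by side and then works out the shift under assumed values.

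**1. Timing.** Randomisation is at about month 2 (Randomization). The four sessions are at weeks 12 to 15 (Table 1). Follow-up weights are at months 6, 12 and 24 (Measurements). The earliest follow-up weight is thus about 6 − 2 = 4 months after randomisation and after all four sessions. Any change computed from the scheduled weights includes time after randomisation. A change restricted to the period before randomisation has no scheduled closing weight.

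**2. Pathway.** Intervention to weight is stated as a possibility (Background), and maintained weight loss is part of the overall goal (Aim). Weight to HRQoL is stated twice (Background, Discussion). Both links of a mediating path are therefore in the document, the first of them only as a possibility.

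**3. Size of the shift.** Code weight change so that better weight maintenance is positive, and work in SD units. Let

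- τ = total effect on HRQoL, set to 0.50 (Power calculations prints d as 50 and calls it moderate; read as 0.50)
- a = arm difference in weight change (not in the document; assumed 0.1 to 0.4)
- β = within-arm regression slope of HRQoL on weight change (not in the document; assumed 0.2 to 0.5)

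In a linear model, adjusted effect = τ − a × β.

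- Low end: 0.1 × 0.2 = 0.02; adjusted effect 0.48; 0.02 / 0.50 = 4% removed.
- High end: 0.4 × 0.5 = 0.20; adjusted effect 0.30; 0.20 / 0.50 = 40% removed.
- No effect on weight: a = 0, shift 0, adjusted effect 0.50.

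**4. Check by simulation.** One million simulated women per scenario, 60/40 allocation, total effect fixed at 0.50. Here b is the causal effect of weight change on HRQoL. An optional unmeasured common cause has loading 0.4 on weight change and 0.3 on HRQoL. With unit within-arm variances the slope is β = b + 0.4 × 0.3 = b + 0.12 when the common cause is present, and β = b when it is absent. The simulations take a up to 0.5, slightly beyond the range in step 3.

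| a | b | Common cause | β | 0.50 − aβ | Simulated adjusted effect |
|---|---|---|---|---|---|
| 0 | 0.5 | no | 0.50 | 0.50 | 0.499 |
| 0 | 0.5 | yes | 0.62 | 0.50 | 0.498 |
| 0.2 | 0.3 | no | 0.30 | 0.44 | 0.439 |
| 0.2 | 0.3 | yes | 0.42 | 0.416 | 0.413 |
| 0.5 | 0.5 | no | 0.50 | 0.25 | 0.249 |
| 0.5 | 0.5 | yes | 0.62 | 0.19 | 0.191 |

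Without weight change in the model, the estimate was between 0.497 and 0.504 in every scenario run. The table also shows that a shared unmeasured cause acts through β. Once β is the observed within-arm slope, that bias is already counted.

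**The case against.** **The sentence is open.** It does not say that the primary model carries weight change. Stratification could mean results displayed by weight-change group, and adjustment could mean an additional model. The definition of the primary analysis that follows does not mention weight. This is a condensed article, and model details are often left to an analysis plan. This stands in part: a reader might infer that the primary estimate is committed to a weight-change-adjusted model, and the text does not go that far. But it applies the rule to the analysis without limit, directly after the main comparison, and names no primary analysis without it. A stated rule that can give the wrong estimate is more than a missing detail.

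**The bias is conditional.** The article says only that the intervention might limit regain, and weight is in neither specific aim. If allocation does not move weight, linear adjustment does no harm. This stands in full, so it would be wrong to say that the estimate will be biased.

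**Other stronger readings do not hold.**
- That weight change is mostly post-randomisation: the article does not say how much of the loss falls in the first two months. Only at least partly follows.
- That the bias has an unknown sign: the article describes HRQoL rising with weight loss and an intervention that might preserve it, which points to attenuation of a true benefit.
- That bias from shared causes is added to the product in step 3: it is already inside the within-arm slope, so adding it would count it twice.

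**Conclusion.** The point holds in conditional form. The plan allows conditioning on a variable that is at least partly post-randomisation and that, by its own account, the intervention may change and HRQoL follows. If the intervention affects weight, the conditioned estimate is not the total effect asked for in the first aim, and the likely direction is attenuation. If it does not, a linear adjustment is harmless.

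Under the assumed inputs the shift is 0.02 to 0.20 SD, or 4% to 40% of a planned effect read as 0.50. The low end is negligible and the high end is not. The document supplies neither factor, so the range illustrates the possible size and does not estimate it. It also takes no account of precision that adjustment might gain. The case for changing the wording rests on the structure of the rule: whether the intervention moves weight cannot be known in advance, and leaving weight change out of the main models gives the total effect either way.

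**What to change.** Replace the sentence in Statistical analyses with wording that does four things:

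1. Estimates the primary HRQoL effect and the main secondary effects without conditioning on post-randomisation weight change.
2. If weight is wanted for precision, adjusts for pre-surgery weight or BMI, both already collected and shown in Table 2.
3. Reports weight change as an outcome, compared between the randomised arms.
4. Labels any analysis adjusted for or stratified by weight change, and any mediation analysis, as exploratory, with its assumptions stated.

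The cost is wording in the protocol or analysis plan. No new data are needed. Follow-up was planned to run to the end of 2019 (Methods and design), so the change could be settled before the 24-month results are analysed.
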